### Professional development about intimate partner violence

Randomised trials with abused women are a controversial issue, because of the ethical concern about what would be withheld to women in the comparison arm. In order to provide all women in the study, comparison women included, with an enhanced primary health care service (one in which health care professionals would all have had training to identify and refer women to family violence or other support services), MOSAIC provided an initial full day's IPV training and resources (manuals, referral booklets, pamphlets), to all participating health care professionals. GP and nurse participation in MOSAIC was contingent on taking part in professional development designed to enhance:

• knowledge about the prevalence and sequelae of partner violence, especially in the childbearing years;

• skills in recognising symptoms of victimisation, perpetration and the impact on children;

• sensitive inquiry about abuse

• a supportive response; and

• effective referral of family members to appropriate services.

The GP training program was informed by a new curriculum and international consensus guidelines developed by two MOSAIC investigators ([name]) to provide GPs with identification and management strategies for all members of the family (victims, perpetrators and children) experiencing partner violence [38]. Professional development points were awarded toward annual accreditation for participating GPs. Interactive adult learning strategies and values-identification were key features of the training program [39]. The program consisted of six hours of:

▪ readings and formal lectures about prevalence and sequelae;

▪ hearing the direct experiences of victim and ex-perpetrator consumer consultants;

▪ small-group discussion about case studies; and '

▪ fish bowl' practice consultations with simulated patients.

Family violence service providers for victims and perpetrators in the region explained their services to GPs. Similarly sessions for MCH nurse teams also involved six hours of interactive learning strategies, readings, presentations, videos, small-group discussion and additional resources for self-learning. While the focus of MCH nurse training was mainly on the needs of abused women, nurses were also interested to explore their role with abusive partners. Following the training, general practices and MCH nurse teams were then randomised.

### Randomisation

GP practices and MCHN teams were randomised at separate public meetings following completion of the professional development programs. For GPs, names (stratified by practice size – one GP or more than one GP participating) were concealed in opaque envelopes and randomly selected by someone outside the study. Similarly names of the MCHN teams were concealed in opaque envelopes, with teams stratified by the number of births in the local government area and the selection made by an invited guest from outside the project or research team. GPs and MCH nurse Team Leaders were present to ensure the fairness of the process and to check the contents of the envelopes prior to their being sealed.

### Blinding

MOSAIC is a pragmatic intervention study. Due to cluster randomisation, it was not possible to blind the health care providers to their status when different processes were required in order to introduce women to the study and refer them to the research team in different arms [21]. Similarly, research staff were not blind to participant status as differing levels of information and follow-up were required for participants in the different arms of the study.

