### The MOSAIC model

#### Mentoring and advocacy

For women identified as abused or at risk of abuse, MOSAIC mentor mothers provided regular contact for up to 12 months. This included:

• Providing non-judgemental listening, support and friendship;

• Maintaining contact (weekly on average) and support through phone calls, home visiting and outings;

• Assistance in developing safety strategies appropriate to women's circumstances;

• Developing a trusting relationship and modelling a sense of hope;

• Providing information and support with parenting; and

• Providing information about, and assisted referral to community services (especially family violence services) and resources for women and their children.

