#### Mentor mother coordination and support

MOSAIC Coordinators were responsible for calling or visiting a woman referred to the intervention arm of the study to assess her situation and her preferences for a mentor. The Coordinator was then responsible for approaching a suitable mentor and arranging a match meeting. While a woman was waiting to be matched, a mentor support officer rang the women to provide them with interim telephone support.

A Coordinator accompanied the mentor to meet the woman and facilitate an understanding of the roles and responsibilities, boundaries, and goals (if appropriate) of the new relationship. This included the option for either woman to agree or not to the match. The Coordinator rang both women 24 hours later to ascertain whether each was keen to continue or not. There were a few times when women expressed the desire for another mentor following an introduction and a rematch was then required. Additionally, a mentor might need to leave the program for unavoidable reasons (e.g. moved interstate, or commenced full-time employment) and a rematch was then required.

Mentors were encouraged to contact a Coordinator when visits with women were challenging, required information which the mentor could not provide at the time, or for any other additional support. All mentors were provided with mobile phones for their personal safety and to ensure that mentors bore no financial costs of contacting women or Coordinators.

The Coordinators conducted and documented four monthly reviews with women to see how the relationship with the mentor was going from the woman's point of view. Participants were also able to contact the Coordinator at any time if they felt the need to talk about how their mentor support was going or to seek additional specialist advice about particular circumstances. Coordinators also regularly reviewed fortnightly contact sheets completed by mentors to monitor progress with the participant. This may have required her contacting the mentor if there had not been satisfactory feedback or contact sheets were not submitted, or if the Coordinator judged that there was any concern for the welfare of the mentor or the participant which required contact.

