### Recruitment and consenting of participants

The participating GPs and MCH nurses were asked to fax, phone or email contact details of women they had identified as eligible (abused or psychosocially distressed and indicative of abuse) and who were willing to participate in a study of emotional support for mothers experiencing difficulties. Research staff then contacted women to arrange for a safe time and place to provide women with more explicit information, negotiate consent, administer a baseline survey and give all women a list of local and statewide resources for mothers, including information about family violence services. In the intervention arm, the research officer then contacted the Coordinator and arranged a suitable time for her to visit. Women whose English rendered them unable to give informed consent (whose language was not Vietnamese) or those with unmanaged serious mental health issues were excluded.

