### Sample size considerations

With 80% power and 95% confidence, MOSAIC aimed to detect a difference of 16% in abuse or depression a year after recruitment. This was originally estimated to require 165 women in each trial arm with individual randomisation. This reduction was thought to be attainable from a level of any prevalence value for either IPV or depression between 30% and 70% in the control group of women already identified by their GPs as abused or at risk. With cluster randomisation, assuming an intra-class correlation of 0.02 (previously found in a GP partner violence study [18]), the sample size required increased to 190 in each arm. Given the mobility of this vulnerable, sometimes fearful population an expected attrition and loss to follow up of as much as 45% could be expected, requiring 350 to be recruited in each arm. Piloting data indicated that 40 weeks would be required for referral and recruitment of this required number of participants.

By May 2007 (well beyond the 40 week period), both referral and recruitment had been slower than expected and the ratio of intervention to comparison for both those referred and recruited was approximately 2:1. At this stage 131 women in the intervention arm and 71 women in the comparison arm had been referred and of these 63% had been recruited. It was decided to extend the recruitment period for another 7 months, and include one additional MCH nurse team in each arm of the trial.

The estimated sample size was recalculated and we then estimated that, for simple random sampling, with 118 in the intervention arm and 64 in the comparison arm, the study would have 80% power and 95% confidence of being able to detect a difference between arms of 22% for IPV, 18% for depression and two units in the mental component score (MCS) of the SF36. Allowing for the overall 37% attrition rate seen to that time and the 10% inflation factor for the cluster sampling, we hoped to achieve total referrals of 206 women (+75) in the intervention arm and 112 (+41) in the comparison arm to be referred in the extra time period.

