### Data collection

Baseline data were collected on recruitment and outcome evaluation data were collected twelve months later. We repeated the two primary outcome measures after twelve months of mentoring in the few instances where there was a delay of three months or more in a participant being allocated a mentor. Any woman who was offered a mentor received a supplementary questionnaire about her experience of mentoring.

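### Contact differs by arm while one loss allowance of up to 45% covers both arms, so loss related to abuse or depression could bias the 12-month contrasts in either direction

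*Protocol article*

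**What the plan says.** **Contact in the intervention arm.** Mentoring and advocacy describes up to 12 months of support, including: "Maintaining contact (weekly on average) and support through phone calls, home visiting and outings". Mentor mother coordination and support adds: "The Coordinators conducted and documented four monthly reviews with women". It also describes interim telephone support for women waiting for a match.

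**Contact in the comparison arm.** At recruitment, research staff were to "administer a baseline survey and give all women a list of local and statewide resources for mothers". Data collection then says: "Baseline data were collected on recruitment and outcome evaluation data were collected twelve months later". The article describes no study contact with comparison women between those two points. The same section provides repeat primary outcome measures after a delayed match and a supplementary mentoring questionnaire, both of which relate to being offered a mentor.

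**Stated asymmetry.** Blinding says that "research staff were not blind to participant status as differing levels of information and follow-up were required for participants in the different arms".

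**Expected loss.** Sample size considerations attributes loss to a population that is mobile, vulnerable and at times afraid: "an expected attrition and loss to follow up of as much as 45% could be expected, requiring 350 to be recruited in each arm". One figure serves both arms.

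**Analysis.** Data analysis and reporting plans an analysis by allocation with adjustment for clustering. It adds multivariable logistic regression because one major prognostic factor was found to be imbalanced. That sentence does not name the factor.

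**The concern.** Twelve-month outcomes come from a survey, so a woman has to be reached to contribute one. Regular contact with a mentor and a Coordinator may keep a woman reachable, and the article describes nothing comparable for the other arm. The article's own reasons for expecting loss, mobility and fear, could plausibly go with continuing abuse or depression.

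If comparison women are lost more often, and lost women differ in outcome from retained women, the two groups with 12-month data are selected differently. Balance at baseline does not protect against that. If lost women are the more abused, heavier comparison-arm loss makes that arm look better and hides a benefit. If they are the less abused, it creates an apparent benefit. Analysis by allocation keeps women in their arm, but women without 12-month data can contribute only through assumptions.

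**Working it through.** **1. The plan's own figures.** Inputs from Sample size considerations: 80% power, 95% confidence (taken as two-sided 0.05), a 16-point difference, control prevalence 30% to 70%, intra-class correlation 0.02.

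- Two proportions with continuity correction: the largest requirement over that prevalence range is 165 per arm, as stated.
- Clustering: 190 / 165 = 1.15, which at 0.02 implies about 8.6 women per cluster.
- Loss: 190 / (1 − 0.45) = 346, against the stated 350.

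The chain reproduces, with the same 45% in each arm.

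**2. The recalculation.** 118 / 0.63 × 1.1 = 206 and 64 / 0.63 × 1.1 = 112, matching the stated referral targets. The 37% used here is 100% minus the 63% of referred women who were recruited, so it is loss before recruitment. The 118 and 64 therefore carry no separate allowance for loss over the 12 months. If 45% of the 114 and 60 women recruited were lost, about 63 and 33 would remain (114 × 0.55 and 60 × 0.55).

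**3. Bias formula.** Let p be the true risk in an arm, L the proportion lost, and d the risk in lost minus retained women. Then p = (1 − L) × r + L × (r + d), so the retained risk is r = p − L × d. With no true effect, the observed intervention-minus-comparison difference is L_C × d_C − L_I × d_I. If d is the same in both arms, this becomes d × (L_C − L_I).

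**4. Illustration, in percentage points.** All loss gaps and risk gaps are assumed; the documents give neither.

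| Loss gap | d = 0 | d = 10 | d = 20 | d = 30 |
|---|---|---|---|---|
| 0 | 0 | 0 | 0 | 0 |
| 5 | 0 | 0.5 | 1 | 1.5 |
| 10 | 0 | 1 | 2 | 3 |
| 30 | 0 | 3 | 6 | 9 |

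A 30-point gap could be 35% v 65%. With 114 and 60 women the overall loss is then (39.9 + 39) / 174 = 45%. A negative d reverses the sign.

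Against the recalculated detectable differences (read as percentage points), 0.5 to 1 point is 2% to 5% of 22 and 3% to 6% of 18. Nine points is 9 / 22 = 41% and 9 / 18 = 50%.

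**5. Relaxing the common d.** Assume 50% true risk in both arms and no effect.

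- Lost women at 60% risk in both arms: the spurious difference is 0 at 45%/45% loss (intervention/comparison), 3.3 points at 40%/50%, 6.8 at 35%/55% and 10.7 at 30%/60%.
- Abused women retained at 0.7 or 0.8 times the rate of other women, the same in both arms: 0 at every one of these splits.
- That ratio at 1.0 in the intervention arm and 0.7 in the comparison arm: 8.8 points, even with equal 45% loss.

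The pattern of loss within each arm matters as well as the amount, so a sensitivity analysis has to vary the arms separately.

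**The case against.** The strongest reply is that the article nowhere says 12-month tracing differed. The Blinding sentence explains why research staff knew the allocation. The follow-up it mentions may mean arranging the Coordinator's visit or the extra mentoring questionnaire. Women in both arms came through GPs or nurses who supplied contact details. A condensed article would commonly leave retention procedures and missing-data methods to the full protocol or SAP, so their absence here is no finding. CONSORT reporting from recruitment is promised and would show losses by arm.

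Much of this stands. A reader might infer that comparison women had no scheduled contact for a year; that is silence in a condensed article, not a statement. A reader might also infer that loss will differ by arm and will bias the result. No retention by arm is given. The 45% is an upper allowance from the original calculation, and mobility and fear describe the whole population rather than a link between loss and 12-month outcome. Unequal loss alone need not bias anything, as steps 4 and 5 show.

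What remains is a stated difference in contact, a large expected loss, and a planned adjustment tied to one factor found imbalanced. Adjusting for that factor need not capture the baseline predictors of loss.

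**Conclusion.** The point holds as a risk. The documents show more contact in the intervention arm, say that follow-up requirements differed, and expect substantial loss with a single allowance for both arms. They do not show that loss differed, that it was related to outcome, or which way any bias would run.

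The size cannot be derived from the documents. With a common risk gap, it runs from zero, through 0.5 to 1 point for modest gaps, to 9 points when both gaps are 30. Nine points is not a ceiling, since other assumptions in step 5 give 10.7. The relevant yardsticks are the recalculated 22% for violence and 18% for depression. The original 16% target belongs to the superseded sample size and would make the bias look relatively larger.

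This does not invalidate the design, but it justifies a small change to the analysis.

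**What to change.** In Data analysis and reporting:

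- Prespecify baseline CAS and baseline EPDS as covariates in all primary outcome models, in place of adjusting only for the one factor found imbalanced. This reduces bias to the extent that loss depends on baseline status. It does not cover abuse or distress arising during follow-up.
- Report 12-month response by arm within baseline CAS and EPDS groups, in addition to the overall losses that CONSORT reporting will give.
- Add a tipping-point analysis that varies the risk in lost women separately by arm and states where the conclusion would change.

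The cost is a little more analysis work and a rule for the few women with a missing baseline score: 1 + 4 = 5 for CAS and 1 + 1 = 2 for EPDS in Table 2. Added contact calls to comparison women are not part of this fix. Ethical and safety issues treats a perpetrator answering the phone as a hazard, and Data collection already reports outcome collection in the past tense.

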### Ethical and safety issues

MOSAIC received ethics approval from the Human Ethics Committee at La Trobe University (03–76) and the University of Melbourne (030441). Safety and confidentiality are priority ethical issues for any study involving victims of IPV [40,41]. MOSAIC safety protocols involved agreed processes to be followed to enhance the safety of participants, staff and mentors, including: assessment of safety prior to visiting women; women's expressed choice of safe location; what to do in any situation where the perpetrator may answer the phone, come home unexpectedly when a mentor or staff member is visiting, or contact or follow MOSAIC staff members. In all cases the protocols aimed to ensure that project activities did not jeopardise participant safety. Additional protocols covered project responsibilities and processes regarding child abuse if this was identified and suicidal ideation if this was reported (see ref. 32 Appendices). All staff had mobile phones and were "buddied" with another staff member to whom they told their leaving time and location and to whom they were asked to report when interviews were complete. Coordinators and mentors were also provided with mobile phones and were trained in safety procedures and making safety plans. As indicated above, we gave all participating health care professionals in either arm extensive IPV training and referral resources so that, we hypothesised, all women in the study would be cared for by well-trained and resourced providers.

### Recruitment and consenting of participants

The participating GPs and MCH nurses were asked to fax, phone or email contact details of women they had identified as eligible (abused or psychosocially distressed and indicative of abuse) and who were willing to participate in a study of emotional support for mothers experiencing difficulties. Research staff then contacted women to arrange for a safe time and place to provide women with more explicit information, negotiate consent, administer a baseline survey and give all women a list of local and statewide resources for mothers, including information about family violence services. In the intervention arm, the research officer then contacted the Coordinator and arranged a suitable time for her to visit. Women whose English rendered them unable to give informed consent (whose language was not Vietnamese) or those with unmanaged serious mental health issues were excluded.

### Ongoing health care provider support

A number of strategies were employed to ensure effective liaison between MOSAIC staff and GP practices and MCH teams. These included: project updates sent via a regular project newsletter; ongoing provision of appropriate posters and pamphlets in relevant community languages as well as in English when requested; offering opportunities for further upskilling following interim process evaluation; facilitating opportunities to meet with local family violence and related services; and providing timely feedback about any referrals made.

### Sample size considerations

With 80% power and 95% confidence, MOSAIC aimed to detect a difference of 16% in abuse or depression a year after recruitment. This was originally estimated to require 165 women in each trial arm with individual randomisation. This reduction was thought to be attainable from a level of any prevalence value for either IPV or depression between 30% and 70% in the control group of women already identified by their GPs as abused or at risk. With cluster randomisation, assuming an intra-class correlation of 0.02 (previously found in a GP partner violence study [18]), the sample size required increased to 190 in each arm. Given the mobility of this vulnerable, sometimes fearful population an expected attrition and loss to follow up of as much as 45% could be expected, requiring 350 to be recruited in each arm. Piloting data indicated that 40 weeks would be required for referral and recruitment of this required number of participants.

By May 2007 (well beyond the 40 week period), both referral and recruitment had been slower than expected and the ratio of intervention to comparison for both those referred and recruited was approximately 2:1. At this stage 131 women in the intervention arm and 71 women in the comparison arm had been referred and of these 63% had been recruited. It was decided to extend the recruitment period for another 7 months, and include one additional MCH nurse team in each arm of the trial.

The estimated sample size was recalculated and we then estimated that, for simple random sampling, with 118 in the intervention arm and 64 in the comparison arm, the study would have 80% power and 95% confidence of being able to detect a difference between arms of 22% for IPV, 18% for depression and two units in the mental component score (MCS) of the SF36. Allowing for the overall 37% attrition rate seen to that time and the 10% inflation factor for the cluster sampling, we hoped to achieve total referrals of 206 women (+75) in the intervention arm and 112 (+41) in the comparison arm to be referred in the extra time period.

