#### ◦ Outcome evaluation

Abuse status was measured using the Composite Abuse Scale (CAS), a comprehensive, well-tested and validated screening tool which discriminates between differing forms of abuse (severe combined abuse, physical abuse only, emotional abuse and harassment) [42]. Depression was measured using the Edinburgh Postnatal Depression Scale (EPDS) [43], which has been validated with mothers (and fathers) outside the immediate postpartum period [44,45]. Women's general health status was measured using the SF36 [36]. The mother-child relationship was measured using the Parenting Stress Index (PSI) Short Form, which can be used for parents of children as young as one month [46] and has been used previously with women experiencing abuse. The PSI Short Form (SF), has three subscales derived from and well validated against the long form: – Parental Distress, Parent-Child Dysfunctional Interaction (P-CDI) and Difficult Child. The P-CDI subscale elicits threat to the parent-child relationship [46]. Use of and satisfaction with GP and MCH nurse care was measured via participant self-report.

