### Sample description

Table 1 below describes participant characteristics in both arms of the trial. There are very few differences in the socio-economic profiles of participants in the two arms of the study. A slightly higher proportion of women in the comparison arm have less than 12 years of education. However, both groups have a high percentage of women with indicators of disadvantage. Over 70% in both arms have a health care card (i.e. government coverage of health care costs for those with inadequate income), over half are dependent on a pension or benefit (e.g. single-parent support), over half have only completed either apprenticeship level, year 12 education or below and while most are Australian citizens, over a third are born overseas. Very few Vietnamese women (n = 4) were referred in the comparison arm.

Table 2 describes the distribution of scores at baseline on primary outcome measures, namely levels of abuse and depression. GPs and nurses identified abused and depressed women to MOSAIC, but at very low levels over the extended two year period. The proportion of women abused (CAS ≥ 7) is comparable between arms (≥ 80%), and the proportion of women abused among those victimised in the previous 12 months (the majority) is equal in both arms (95%). The proportion of women depressed (EPDS ≥ 13) is higher in the intervention arm than in the comparison arm, with a difference in mean baseline EPDS score (15.4 in the intervention arm, 13.0 in the comparison arm).

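### The recalculated detectable differences for depression (18 points) and MCS (two units) hold only under favourable values that the protocol article does not state

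*Protocol article*

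**What the plan says.** All the planning figures are in the protocol article under Sample size considerations. The first calculation aimed at a 16-point difference in abuse or depression at one year, with 165 women per arm before clustering, and was said to cover "any prevalence value for either IPV or depression between 30% and 70% in the control group".

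After slow and unbalanced recruitment the calculation was redone "for simple random sampling, with 118 in the intervention arm and 64 in the comparison arm". With those numbers, "the study would have 80% power and 95% confidence of being able to detect a difference between arms" of the sizes given: "a difference between arms of 22% for IPV, 18% for depression and two units in the mental component score (MCS) of the SF36". The referral targets of 206 and 112 then follow, "Allowing for the overall 37% attrition rate seen to that time and the 10% inflation factor for the cluster sampling".

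The recalculation names no control prevalence for either binary outcome and no SD for the MCS. The Outcome evaluation section says only that "Women's general health status was measured using the SF36". For depression at baseline, Table 2 gives 55% in the comparison arm and 71% in the intervention arm, and the Sample description notes: "The proportion of women depressed (EPDS ≥ 13) is higher in the intervention arm than in the comparison arm".

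**The concern.** IPV and depression are both binary, share the same arm sizes and power, and in the first calculation shared one prevalence range and one target difference. In the recalculation they differ by four points, and no input is given that would explain this. The MCS figure is in raw score units, which cannot be checked without an SD, and the SD it implies turns out to be small.

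Readers use these figures to judge what the shrunken trial could still show. If the unstated inputs are optimistic, the trial looks more sensitive than it is for depression, a primary outcome, and for the MCS.

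**Working it through.** **Inputs.** 118 intervention and 64 comparison women, 80% power, 95% confidence (two-sided 5% assumed, as sidedness is not stated), all from Sample size considerations. The control range of 30% to 70% is from the same section. Baseline depression of 55% in the comparison arm is from Table 2. The MCS SD is not in the document; 10 is a working assumption, shown with a range of 8 to 12.

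**1. The first calculation, to identify the method.** For 16 points with equal arms, the usual two-proportion formula peaks at about 152 per arm (control 58%). With continuity correction, n/4 × [1 + √(1 + 4/(n × d))]², this becomes 152.1/4 × [1 + √(1 + 4/(152.1 × 0.16))]² = 164.4, which rounds up to the stated 165. So the stated figure matches a continuity-corrected calculation at the worst case within 30% to 70%.

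**2. MCS.** Detectable difference = (1.96 + 0.842) × SD × √(1/118 + 1/64) = 2.802 × 0.1552 × SD = 0.435 × SD. Setting this to 2 gives SD = 2/0.435 = 4.60.

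| Assumed SD | Detectable difference (units) | Power for 2 units |
|---|---|---|
| 6 | 2.6 | 57% |
| 8 | 3.5 | 36% |
| 10 | 4.3 | 25% |
| 12 | 5.2 | 19% |

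Baseline adjustment reduces the SD to SD × √(1 − r²). Reaching 4.6 needs r = √(1 − (4.6/SD)²), which is 0.82 at SD 8 and 0.89 at SD 10. The sample size section mentions no such adjustment.

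**3. Depression and IPV.** Power for a reduction d from control prevalence p is Φ{[d − 1.96 × SE₀]/SE₁}, where SE₀ uses the pooled proportion and SE₁ the separate ones. Example with p = 0.55 and d = 0.18: the intervention proportion is 0.37 and the pooled proportion (118 × 0.37 + 64 × 0.55)/182 = 0.433, so SE₀ = 0.0769 and SE₁ = 0.0764. Power = Φ[(0.18 − 0.1508)/0.0764] = Φ(0.38) = 65%.

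| Control prevalence | Power for 18 points | Detectable reduction (points) | Same, continuity-corrected |
|---|---|---|---|
| 30% | 83% | 17.3 | 18.4 |
| 40% | 72% | 19.6 | 20.7 |
| 50% | 66% | 21.0 | 22.1 |
| 55% | 65% | 21.4 | 22.5 |
| 60% | 64% | 21.6 | 22.7 |
| 70% | 66% | 21.3 | 22.5 |

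Without correction, power for 18 points reaches 80% at a control prevalence of 32.5% or below, and again at about 88% or above.

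The 22-point IPV figure reproduces. The largest uncorrected detectable reduction at any prevalence is 21.6 points, and the corrected value is 22.1 at 50%.

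**4. Could another convention explain 18?** One-sided testing gives 18 points at about 43% control prevalence. IPV would then need at most 19.2 points, so one-sided testing does not account for both figures.

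**5. Referral targets.** 118 × 1.10/0.63 = 206 and 64 × 1.10/0.63 = 112. Both reproduce, so the 10% cluster allowance has already been added on top of 118 and 64.

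**The case against.** A reader might infer that the trial cannot detect these differences and that the two figures are arithmetic errors. The documents do not support that.

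- **Depression.** The figure is roughly recovered at 30% control prevalence, inside the article's own range: 17.3 points uncorrected and 18.4 corrected. One continuity-corrected method would give 165 per arm, about 22 points at 50% and about 18 at 30%. Nothing shows that these prevalences were the ones used, but a figure that can be reached within the stated range is not a miscalculation.
- **Baseline rate.** The 55% was measured at recruitment. The relevant quantity is the comparison-arm rate at 12 months, which is not given and could be lower.
- **MCS.** The judgement depends on an SD that the document does not contain, and a condensed article may leave such a value to the full protocol. From the text alone, two units can be neither reproduced nor refuted.
- **Consequence.** What a null result rules out is set by the confidence interval, not by a planning difference. The MCS is not among the primary outcomes listed under Data analysis and reporting. Table 1 already reports 114 and 60 women, so no design decision changes.

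All of this stands, and it limits the point to undisclosed, favourable assumptions. It does not remove it. The first calculation claimed its difference for the whole 30% to 70% range, whereas the 18-point figure fails over nearly all of that range and nothing tells the reader so. A difference in score units published without its SD cannot be assessed.

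**Conclusion.** The point holds as one about unstated and optimistic inputs.

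For depression, 18 points at 80% power needs a 12-month control prevalence of about one third or less (or about 88% or more). Over 50% to 70% the detectable difference is about 21 to 22 points, or 22 to 23 with the correction that reproduces 165 per arm, and power for 18 points is about 65%. This part rests only on the article's own numbers and two-sided 5% testing.

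For the MCS, two units needs an SD of about 4.6, less than half the working value of 10. The shortfall (power of 19% to 36%) is conditional on the assumed SD of 8 to 12. The IPV figure is sound.

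**What to change.** Under Sample size considerations:

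1. Restate the depression difference as about 21 to 22 points (22 to 23 if continuity-corrected), so that it holds across the 30% to 70% range. Alternatively, keep 18 and say explicitly that it assumes a control prevalence of about 30%.
2. Replace the two MCS units by 0.435 times the trial's own baseline MCS SD, and print that SD. With an SD of 10 this would be about 4.3 units.

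No further cluster correction of the 118 and 64 is needed, because the 10% inflation is already in the referral targets. The cost is a short recalculation and a few words. The downside is that the stated figures become less favourable.
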